## Methods/Design

### Study design

The *Cry Baby* trial is a randomised, controlled, superiority trial with two parallel groups (Fig. 1). We adhered to CONSORT guidelines in the design of the trial [44].

**Fig. 1 Fig1:**
[figure not shown]
CONSORT Trial Flow Diagram

### Study setting and recruitment

Participants will be primary carers of infants aged 2 to 12 weeks, recruited by one of two recruitment modalities: advertising on the Raising Children Network (www.raisingchildren.net.au), or recommendation from their MCH nurse. The Raising Children Network website is a non-commercial, evidence-based, quality assured, government-funded online resource that covers a broad range of parenting topics and had over 5.7 million visits in the 2013 calendar year (personal communication). A notice will be placed on relevant pages on the Raising Children Network, as well as its social media (e.g., Facebook, Twitter). This notice will contain a link to the study website where parents can gain more information and take part in the program if desired.

Recruiting some of our sample from Australian wide online advertising and some from a specific region, introduces systematic differences to the groups. In an attempt to reduce this as much as possible, we selected the Melbourne (state of Victoria, Australia) Local Government Area (LGA) of the City of Yarra for MCH nurse recruitment, due to both its high birth rate per annum [45], and broad cultural and socioeconomic diversity [46]. All MCH nurses within this LGA (11) will invite parents of infants attending the 2 week appointment to participate in the trial. The 2 week appointment will be specifically targeted as it was suggested by the nurses that this appointment is less intensive than the in-home appointment at 7–10 days postpartum, and it is unusual for parents of infants aged less than 2 weeks to request information on infant sleep and crying so soon after birth. Recruitment will run for a 12 week period and will allow for later determination of the percentage of parents in the general community that are likely to take part in an online program if suggested by their MCH nurse (birth rate data for this region, throughout this time period will be compared to our sample). MCH nurses will provide parents with a postcard, inviting them to participate in the program. The postcard will contain brief information about the study and a link to the study website so they can gain further information about the research. Participants who indicate that they heard about the Cry Baby program via their nurse *and* via online advertising will be classified as having been recruited via their nurse since it is the effect of encouragement from a health professional that we aim to examine. The Cry Baby program is currently only available to those willing to take part in the research trial and has not been broadly advertised outside the Raising Children Network. This means it is very unlikely that parents would have the program suggested to them by other health professionals.

### Sample size and condition allocation

Power analysis using Stata 13.0 [47] was conducted in order to determine the required sample size for the study. There is no prior published data on our primary outcome (‘use of program strategies’). We have based our estimate of the required sample size on the mean total ‘strategy use’ score of the first 20 participants to be randomised to the control (Cry Baby without email prompts) condition (M = 62.53, SD = 6.04). A clinically relevant shift in the mean ‘strategy use’ score of the Cry Baby plus email prompt condition, would be half a standard deviation away from the control group mean. Based on this data, a 2 group comparative study would require a total sample size of 126 participants (63 in each arm) to have 80 % power to detect a statistically significant finding at p <.05 and a moderate effect size. Allowing for a 20 % drop out rate, we aim to recruit 152 parents.

Participants will be randomly assigned to either the *Cry Baby Only* or the *Cry Baby with Additional Email Prompts* condition, with a 1:1 allocation as per a computer generated randomisation schedule, performed as a simple randomisation. Participants will be randomised using a feature within the online survey program, which offers an online, central randomisation service. Allocation concealment will be ensured, as the service will not release the randomisation code until the participant has been recruited into the trial, and baseline measures have been completed.

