One way this imbalance may be addressed is for infant health care providers to encourage participation. In the Australian state of Victoria all newborn infants are assigned a Maternal and Child Health (MCH) nurse, who provides free health checks at 7 to 10 days, 2 weeks, and then at 1, 2, 4, 8, 12, 18, 24 and 42 months of age. Access is almost universal – 98 % of infants participate in the first (in-home) visit, and 96.6 % attend the MCH clinic for the 2 week (infant age) check up [30]. MCH nurses are in a unique position to direct parents to suitable evidence-based online interventions that are specific to the first few weeks postpartum, because they have frequent contact with parents during this time. In addition, evidence suggests that support or encouragement from nurses or other health professionals during online program participation helps to keep parents engaged [31, 32]. A strategy often employed to increase engagement and retention to online programs, is the use of email prompts, however, little research has specifically examined their effectiveness. Email prompts have been shown to increase the number of adults who returned to computer tailored lifestyle interventions (targeting smoking behaviour and fruit and vegetable intake, for example) [33], and this effect was increased when the prompt occurred soon (2 weeks) after initial program login [34], but we can find no research that evaluates the usefulness of email prompts in samples of parents of infants, whose needs and time demands would be quite different. Uptake of, and retention to, online programs varies considerably, but is generally reported to be lower than anticipated (~2–10 % and ~15–97 %, respectively) [35–39]. If online interventions are intended to be used broadly, then evidence for strategies employed to engage and retain participants, will be necessary.

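### The 20% dropout allowance multiplies by 1.2 instead of dividing by 0.8, so 152 recruits leave about 122 rather than 126 completers and power is about 79%, not 80%

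*Protocol article*

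**What the plan says.** The section on sample size and condition allocation takes the control mean and standard deviation from the first 20 participants randomised to the program without prompts ("M = 62.53, SD = 6.04"). It defines the difference of interest as one that "would be half a standard deviation away from the control group mean". On that basis a two-group comparison "would require a total sample size of 126 participants (63 in each arm"). The operating characteristics claimed for that number are "80 % power to detect a statistically significant finding at p <.05 and a moderate effect size". The next sentence allows for 20% loss and sets the recruitment aim: "drop out rate, we aim to recruit 152 parents". No other section gives a different target or dropout rate.

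**The concern.** The required number, the dropout rate and the recruitment target stand next to each other and do not agree. Dropout is a fraction of those recruited, so the target has to be the required number divided by the fraction retained. Adding 20% to the required number gives too small a target, because the loss is then taken from a larger base. At the dropout rate the plan itself assumes, the trial would end with fewer completers than the plan says it needs, and the power stated for the primary outcome would not quite be reached. What is at stake is the accuracy of the sample-size statement and a small amount of power. The choice of outcome, comparison or analysis is not affected.

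**Working it through.** **Inputs, all from the sample-size section:** SD 6.04; difference 0.5 SD = 3.02 points; significance level 0.05; power 80%; 1:1 allocation; dropout 20%; required total 126; target 152. The section does not say whether the test is one- or two-sided. Two-sided is assumed, because it reproduces the stated 63 per arm, whereas one-sided gives 50.

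**1. Reproduce 126.** Normal approximation:

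n per arm = 2 × ((1.960 + 0.842) / 0.5)² = 62.8, so 63 per arm and 126 in total. This matches the plan.

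**2. Reproduce 152.**

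- Multiplying: 63 × 1.2 = 75.6, so 76 per arm and 152 in total (equivalently 126 × 1.2 = 151.2). This matches the plan.
- Dividing: 126 / 0.80 = 157.5, so 158 in total (79 per arm). This does not match.

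Of the two methods, only multiplying by 1.2 gives the stated target.

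**3. Apply the plan's own dropout to 152.**

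- Expected completers: 152 × 0.80 = 121.6, about 122, or 60.8 per arm.
- Shortfall against 126: 126 − 121.6 = 4.4 completers.
- Shortfall in the target: 158 − 152 = 6 recruits.
- Check on 158: 158 × 0.80 = 126.4, which meets 126.

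**4. Power**, using the same approximation as step 1, Φ(0.5 × √(n/2) − 1.960):

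| Completers per arm | Power |
|---|---|
| 63 (as required by the plan) | 80.1% |
| 60.8 (152 recruited, 20% lost) | 78.7% |

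The difference is 80.1 − 78.7 = 1.4 percentage points.

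**5. Dropout that 152 can absorb.** 1 − 126/152 = 26/152 = 17.1%. The target allows for 26 losses, whereas 20% of 152 is 30.4.

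**The case against.** The strongest reply is that this hardly matters, and on size that is right. The loss is about 1.4 points of power, the 20% is only a planning assumption, and the procedures provide for up to three reminders at follow-up. The number 152 is an aim: recruitment runs for 12 weeks in each modality, and nothing in the article says enrolment stops at 152. All analyses are also to control for child age. If age explained about 3.5% of the outcome variance (1 − 121.6/126 = 3.5%), that would make up the gap. The documents give no such figure, so this shows only how small the gap is. These points settle the severity, but they leave the printed figures inconsistent.

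A second reply is that the planned Full Information Maximum Likelihood analysis recovers the loss. It does not clearly do so. Strategy use is asked only in the follow-up questionnaire, and the baseline questionnaire collects demographic and infant characteristics, so a participant lost to follow-up contributes no value of the primary outcome.

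Two stronger readings are tempting, and the documents support neither:

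- **That 63 per arm is itself wrong.** A reader might note that a two-sample t-test needs 64 per arm. The section names no test, 63 reproduces exactly under the normal approximation, and the planned analysis is not a plain t-test. The difference is a choice of approximation.
- **That power could collapse.** The background says "Uptake of, and retention to, online programs varies considerably, but is generally reported to be lower than anticipated" and cites retention of about 15–97%. A reader might infer very low power from the bottom of that range. The range describes other online programs, and the article does not present it as a forecast of non-response to this trial's follow-up questionnaire. It does not bear on an arithmetic slip at a stated 20%.

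**Conclusion.** The recruitment target is wrong as written. It multiplies by 1.2 where it should divide by 0.80, so at 20% dropout 152 recruits yield about 122 completers instead of 126, and power is about 79% instead of the stated 80%. The target is 6 recruits short of 158. This is a minor but certain error, because it follows from the plan's own figures. The power figures assume a two-sided test, the normal approximation throughout, an effect of exactly 0.5 SD, equal arms after loss, and no primary-outcome information from participants lost to follow-up. A reader should not conclude that the trial is materially underpowered: the shortfall against the plan's own requirement arises only if dropout exceeds about 17%, and at 20% it is small.

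**What to change.** Correct the sentence in one of two ways, using one method throughout:

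- **Keep 152** and state that it gives about 79% power at 20% dropout, and retains 126 completers only if dropout is at most about 17% (normal approximation). The cost is one sentence and a slightly less favourable power figure, with no added recruitment.
- **Restate the target as 158**, which leaves 126.4 completers at 20% dropout. The cost is an aim of 6 more recruits. It also changes the sample size, which the ethics section lists among the modifications that need a formal amendment.

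The required 126, the effect size and the planned analysis need no change on this account.

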### Eligibility criteria

Participants will provide informed consent online (by selecting a checkbox that appears after the Information Statement and before the baseline questionnaire), before any study procedures occur. All parents of newborn infants aged less than 12 weeks, who access www.raisingchildren.net.au or who are seen by their MCH nurse at their 2 week check in the City of Yarra will be invited to participate in the study. However, parents will be excluded from the study if they are under the age of 18 years, have a child over the age of 12 weeks at the time of enrolment into the study, have insufficient English comprehension to complete the questionnaires, have an infant born before 33 weeks gestation, or if the parent and/or infant suffer from a serious medical condition.

### Intervention

Eligible participants, who have completed baseline measures, will be randomised to the *Cry Baby Only* or the *Cry Baby with Additional Email Prompts* groups. The online *Cry Baby* program covers evidence-based information and strategies on parent self-care (e.g., taking care of your body, parent sleep, postnatal depression), infant crying (e.g., why crying is normal and healthy, why babies cry, how to cope with crying) and infant sleep (e.g., infant sleep cycles and cues, settling your baby, safe sleep conditions). All content is delivered within the online platform. The program is brief, taking no longer than an hour to complete. The program has inbuilt activities, for example, parents can move objects to make a cot a safe place for a baby to sleep, they can also ‘burst’ bubbles (using the mouse pointer) to bust common myths about baby care. There is a video showing how to wrap (swaddle) a baby for sleep, links to a coping plan for parents who are feeling overwhelmed by persistent infant crying, as well as links to local parenting support services.

Participants allocated to the *Cry Baby Only* condition will receive log in details to the *Cry Baby* program. Participants can log in or out of the program whenever they please and can move around different areas of the program according to their interests and requirements. If participants decide to complete the program in one sitting it will take approximately 1 hour to finish. The program is designed to be accessed during the first 6 to 8 weeks post-partum, as this is the time when infant crying is most frequent and the advice offered may be most useful. However, we will allow parents of infants up to 12 weeks of age to take part, as evidence indicates that infants who are very unsettled (this may continue after the usual peak in crying has subsided) are at increased risk for AHT [48]. The Cry Baby program may be useful for these parents, and gathering data from those with babies aged 8–12 weeks, will allow for later determination of the age at which parents find the program most useful.

Participants who are randomly allocated to the *Cry Baby with Additional Email Prompts* condition will receive access to the *Cry Baby* program and brief, weekly email prompts from the research team. These messages will contain evidence-based, age appropriate information on infant sleep and crying and parent self care, that is already provided within the online *Cry Baby* program. The email prompts will also direct participants back to the program for more detailed information. As above, participants will be encouraged to access the program before their infant is 6 to 8 weeks of age (when possible), and are encouraged to revisit the *Cry Baby* program as often as needed.

Participants may withdraw from the study at any time for any reason. Likewise, participants allocated to the *Cry Baby with Additional Email Prompts* condition may withdraw from receiving the additional email prompts at any time.

### Outcome measures

Our primary outcome measure will be the frequency with which participants use the strategies recommended in the program (see description of the Follow-Up Questionnaire below). This will be compared across recruitment mode (recruited via the Raising Children Network or via MCH nurse) and trial arms (Cry Baby only versus Cry Baby with Additional Email Prompts conditions).

Secondary outcome measures include: retention to the program at follow up; program completion rates (indicated by every module of the program having been accessed); participant demographic characteristics; infant characteristics; whether the participant would recommend the program to family/friends; report of infant sleeping, crying and feeding problems; average time the infant spends awake during each night waking; and, parent depressive symptoms, fatigue and cognitions surrounding infant sleep.

#### Baseline questionnaire

The participant will be asked to complete a baseline questionnaire online. This will collect demographic information about the parent (age, gender, educational attainment, employment status, country of birth, main language spoken at home, and household income) and infant (birth order, date of birth, gender, birth weight, gestation, and where the baby sleeps at night). Area-level socioeconomic disadvantage will be determined using the *Socio-economic Indexes for Areas* [46] based on participant postal code and population census data.

#### Follow-up questionnaire

A secure web link to the follow-up questionnaire will be emailed to participants when their infant is 16 weeks of age. This represents an age at which most infants ‘sleep through the night’ (i.e., achieve 5 consecutive hours of uninterrupted sleep during the night) [49].

##### Parental use of intervention

A series of questions were developed specifically for the current study. Participants will be asked how often they use the settling (8 items), safe sleep (3 items), and parent wellbeing (5 items) components of the intervention on a 5-point scale, 1 = *Never* to 5 = *All the time*. Mean scores will be computed for the three types of intervention strategies. Participants will also be asked whether they would recommend the program to friends or family, how much of the program their partner participated in (watched/listened to: none/small amount/around half/most/entire program), what was the best part of the program and how could the program be improved.

##### Caregiver support

Participants will rate the level of support or help they received from (1) their partner, (2) family and friends living elsewhere (i.e., I get enough help, I don’t get enough help, I don’t get any help, I don’t need any help), and (3) how often they feel they need support or help but can’t get it from anyone (i.e., very often, often, sometimes, never, I don’t need it) [50]. These items have previously been used in the Longitudinal Study of Australian Children [50] and in the *Baby Business* trial [3].

##### Infant behaviour

Participants will be asked whether infant daytime sleep, night-time sleep, feeding or crying behaviours have been a problem over the last 2 weeks (0 = *No*; 1 = *Yes*). If participants indicate that any of these infant behaviours are a problem, they will be asked to rate the extent on an 8-point scale, 1 = *Hardly a problem* to 7 = *Severe problem*. These items have been used in prior infant sleep research [3, 51].

Additional items will examine: the average number of times per night the participant attends to their infant (1–10+); at each attendance, the number of minutes the participant spends with their infant (<10mins – 2 h); and the average number of feeds the infant has over a 24 h period (items previously used [3]).

##### Postnatal depression

Symptoms of depression will be assessed using the Edinburgh Postnatal Depression Scale [52], a 10 item validated screening tool for PND [53, 54]. Clinically significant levels of depressive symptoms are indicated by scores ≥ 10 and ≥ 9 for mothers and fathers, respectively, in community samples.

##### Fatigue

Both the Fatigue Assessment Scale [55] (FAS) and the Fatigue Severity Scale [56, 57] (FSS) will be used to assess participants’ levels of fatigue. The FAS is a 10 item measure that will be used to assess the physical and cognitive symptoms of fatigue. Items are rated on a 5-point scale (1 = *Never* to 5 = *Always*), where higher scores indicate higher levels of fatigue. The scale has good reported psychometric properties and has been validated for use with parents [58]. The 9 item FSS assesses the intensity of fatigue and associated functional limitations caused by fatigue. Items are rated on a 7-point scale (1 = *Strongly Disagree* to 7 = *Strongly Agree*), where higher scores reflect higher levels of fatigue.

##### Parental cognition around infant sleep

Four subscales of the Maternal Cognitions about Infant Sleep Questionnaire [59] will assess participants’ cognitions about their infants’ sleep. These subscales measure limit setting (e.g., ability to resist infant demands and not be overintrusive in helping the infant fall asleep; 5 items), anger (e.g., anger, regret, and helplessness; 5 items), doubt (e.g., uncertainty regarding ability as a parent; 5 items), and safety (e.g., excessive concerns about cot death; 2 items). Items are rated on a 6-point scale, ranging from 0 = *Strongly disagree* to 5 = *Strongly agree*.

##### Online program usage

Data will be collected via the programming of the online system, recording whether the program was completed (if all program modules were accessed for a minimum of 1 min each), how many times the participant logged in to the program, and how much time in total they spent within the program.

### Procedures

The recruitment phase will run for 12 weeks in each recruitment modality. An advertisement placed on the Raising Children Network will provide interested parents with a link to the program’s online landing page. MCH nurses will provide all parents of newborn infants at the 2 week infant check with an advertising postcard containing the link to the landing page.

The landing page will provide more information describing the study, what participation involves, and a secure link to the online baseline survey where participants can read the projects’ plain language statement and complete eligibility criteria and consent. After completion of the baseline survey, participants will receive email notification of their allocation to condition (i.e., *Cry Baby* alone or *Cry Baby with Additional Prompts*). The final page of the baseline survey will provide participants with a secure link to the *Cry Baby* website, where they can register their login details and immediately access the *Cry Baby* program.

All participants will receive a welcome email which contains further information about the program and their group allocation. Participants allocated to the *Cry Baby with Additional Prompts* condition will also receive a brief, age-appropriate email prompt each week (from 2 weeks of infant age) until their infant reaches 12 weeks of age. Each email will contain a brief summary of information from the online program.

When participants’ infants are approximately 16 weeks of age, they will receive an email link to the follow up survey which has their unique ID code embedded. If participants have not completed their follow-up questionnaire after 2 weeks, a reminder email will be sent a maximum of three times over a 6 week period. At this time point, some parents will only have had access to the program for 4 weeks, and others for 14 weeks, however, we expect that if parents are going to try out strategies suggested in the program, they would do so within 4 weeks of their first access to the program. Setting the follow up time point according to infant age, rather than time since enrolment, controls for the large variability in infant development that might otherwise impact on our results.

